#### Compensation and incentives

Participants will be compensated for their time spent at the research facility, their traveling costs and efforts with a monetary value of $50 per visit. Participants randomized to the intervention group will also receive all free meals for a period of 8 to 12 weeks depending on their fertility treatment plan. They will also receive training assistance, coaching, and reimbursement for monthly fees to a gym of their choice up to $50/month for the duration of the intervention. As an incentive to keep up with the exercise intervention, participants will be offered $10/week for meeting their step and exercise goal. A bonus of $80 will be provided to participants who completed all weekly exercise sessions prescribed. Participants in the standard of care group will receive a completion bonus with a monetary value of $200 at their last visit. Total compensation for the standard of care group (all paid by checks or gift cards) will be up to $350 dollars.

### Data collection, management, and analysis

#### Data collection methods

Participants will attend three research study visits at the ACNC, two at the beginning of their fertility procedures and the last within 5 days of their oocyte retrieval procedures. Table 1 and Fig. 1 detail the time schedule of enrollment, participant visits, and the intervention. On average, we anticipate that there will be 8–12 weeks between visit 1 and 3 depending on the participant’s fertility treatment plan. Questionnaires will be administered on paper or via online platforms such as RedCap.

##### Background information and releases

Women who agree to participate will provide background information including their name, address, date of birth, education, number of people living in their household, marital status, and health history. Participants will be required to obtain an exercise release form from their physician at AF&GA prior to the study visit. They will also be required to sign a consent for release of medical information in order to obtain data relating to the clinical results from the fertility procedures as well as pregnancy and delivery outcomes.

##### Anthropometrics and vitals

Anthropometric data will include height, weight, and waist and hip circumferences. All measures will be repeated in duplicate or triplicate in order to ensure measures fall within stated tolerance ranges. Height will be measured to the nearest 0.1 cm with a wall-mounted stadiometer (tolerance of +/− 1 cm). Weight will be measured to the nearest 0.1 kg on a scale that has been tared with clothing the participant is wearing (tolerance of +/− 0.1 kg). Waist and hip circumferences will be measured to the nearest 0.1 cm using a tape measure against bare skin or form fitted shorts (tolerance of +/− 1 cm).

Vitals will include blood pressure, pulse, and temperature. Blood pressure and pulse will be measured with a digital blood pressure monitor twice (with 5 min in between each measurement); a third measurement will be taken if the two measures have a difference of 6 mmHg for systolic or 4 mmHg for diastolic blood pressure. Temperature will be taken upon arrival for each visit with an infrared non-contact forehead thermometer in accordance with COVID-19 screening procedures. Participants with a temperature ≥ 100.4 °F will be asked to reschedule their visit while those with a temperature below 100.4 °F will have it taken again orally with a SureTemp Plus thermometer for data collection purposes.

##### Body composition

Body composition and bone mineral content will be measured using dual energy X-ray absorptiometry (DXA; Hologic Horizon A, Bedford, MA). This technology involves very small amounts of radiation and yields a very important measure of body composition and bone mineralization [32]. Quality control calibrations will be performed each day and subjects will be positioned according to the manufacturer recommendations for the whole body scan while wearing light clothing without metal.

##### Resting and activity energy expenditure

Resting energy expenditure will be measured using indirect calorimetry (MOXUS, AEI technologies, IL) following an overnight fast while wearing a heart rate monitor (Polar, Finland) [33]. The instrument measures the flow of oxygen consumed and the flow of carbon dioxide produced to calculate energy expenditure. The system will be calibrated daily. Activity energy expenditure will be assessed using the ActiGraph 9XLink accelerometer (ActiGraph, Pensacola, FL) worn for 7 days and a previously validated physical activity questionnaire (International Physical Activity Questionnaire) [34].

##### Fitness and leg strength tests

A cardiorespiratory fitness test will be performed on a treadmill following the guidelines for exercise testing from the American College of Sports Medicine. After evaluating the participant at rest and during the 3–5 min warm up, speed and/or incline will be increased in periods until exhaustion. During the entire test, breath composition will be sampled and measured using a metabolic cart (Medgraphics Ultima PFX® system, MGC Diagnostics Corporation, St. Paul, MN, USA). Leg strength will be measured by an isokinetic dynamometer (Humac Norm, Computer Sports Medicine Inc., Stoughton, MA). The Humac dynamometer will be used for testing of right and left legs for flexion (hamstrings) and extension (quadriceps) at certain angular velocities.

##### Biological samples

Blood samples, up to 35 ml, will be collected from the participants at visits 1 and 3 by a trained phlebotomist under overnight fasted conditions. During the entire study, we will collect up to 70 ml total. Blood samples will be centrifuged to separate plasma, serum, and red blood cells. Blood samples will be used to assess glucose, insulin, HOMA-insulin resistance score, interleukin-6, C-Reactive Protein, tumor necrosis factor, leptin, lipid profiles or any other biomarkers or analytes of interest using ELISA, electrochemiluminescence (ECL), colorimetric assays, metabolomics or any other appropriate methodology. Urine and stool collection will be obtained to evaluate metabolites, hormones or bacteria/microbes. Samples will be obtained using sterile collection cups. All biological samples will be aliquoted and stored at − 80 °C until further analyses.

##### Depression and perceived stress

Maternal depression will be evaluated using the Beck Depression Inventory-II, which has been shown to have high reliability and validity [35]. Participants’ level of perceived stress will be evaluated through the administration of the Cohen’s Perceived Stress Scale which is a validated 14-item questionnaire examining the perception of stressful life events and levels of experienced stress over the course of the 4 weeks prior to the completion of the survey [36]. Participants with elevated scores will be provided with mental health resources and referred to their primary care provider.

##### Dietary assessment

Baseline dietary intakes will be assessed using 3-day food records. Dietary data will be evaluated by a trained research assistant for completeness and analyzed with the Nutrition Data System for Research (NDSR, Nutrition Coordinating Center, University of Minnesota, MN). Data entry into this software will be randomly audited (10%) by a trained research assistant to ensure quality control.

##### Oocyte, cumulus cell, and follicular fluid data collection

AF&GA will provide the research team with oocytes (eggs), cumulus cells (cells surrounding the egg), and follicular fluid (liquid surrounding the egg that also contains granulosa cells) that are not needed for the IVF procedures (e.g., too many eggs retrieved). These samples will be collected during the standard oocyte retrieval procedures performed as part of standard care for the participants undergoing fertility treatment. Participants will undergo standard procedures at AF&GA for ovarian stimulation, which include hormonal superovulation and oocyte retrieval 36 h after human gonadotropin injection. Any deviations from the standard clinic procedures will be documented and sensitivity analyses will be performed to determine whether deviations to stimulation protocol yielded in significant differences. It is possible that the research team will not obtain samples in the case that the retrieval yields only enough eggs for the IVF procedures. In this case, only follicular fluid will be obtained. The research team will not obtain samples that could have been fertilized or frozen as agreed with the participant prior to the retrieval procedure. The research team will obtain only samples that are unneeded by the clinic. Thus, no additional treatment or clinical procedures will be required for the participants. The embryologist at the clinic will collect the cumulus cells during the processing of the oocytes. Granulosa cells will be isolated from the follicular fluid by centrifugation at 4000 rpm for 10 min. Follicular fluid samples contaminated with blood will not be used for analysis. Samples will be placed on ice and transported by the research team to the ACNC where they will be stored in messenger RNA lysis buffer and frozen at − 70 °C until processing. Oocytes and cumulus cells will be used to study gene expression while follicular fluid will be used to measure metabolites and hormones that may be influenced by diet and exercise. Both mRNA and genomic DNA will be isolated from individual oocytes as previously described [9]. cDNA libraries will be prepared and fragmented cDNA will be evaluated to determine size distribution of the libraries. Samples will be sequenced using the NextSeq 500 System (Illumina). Individual libraries will be generated and RNA-Seq will be conducted. Sequencing reads from each sample will be trimmed and filtered before being aligned to the human genome (hg19). All data will be analyzed using SeqMonk and R software. Differentially expressed gene expression will be identified using the DESeq2 package which will include multiple testing corrections. Serum and follicular fluid glucose, total cholesterol, and triglyceride levels will be assessed using colorimetric or electrochemiluminescence assays. Serum and follicular fluid insulin, leptin, tumor necrosis factor (TNF)-α, C-reactive protein (CRP), and interleukin-6 will be measured using enzyme-linked immunosorbent or electrochemiluminescence assay kits. Serum lipid profiles—non-esterified fatty acids, high-density lipoprotein, and low-density lipoprotein— will be analyzed by enzymatic methods on a clinical analyzer. All assays will be performed in accordance with the manufacturers’ instructions.

##### Feasibility and acceptability

Feasibility and acceptability will be measured primarily through structured qualitative interviews that will take place after intervention completion. These interviews will be conducted by trained team members in-person or virtually through video conferencing and are expected to last approximately 60 min. They will be audio recorded and transcribed before being coded and analyzed to identify key factors contributing to feasibility and acceptability of the intervention. Compliance with the intervention provides another measure of feasibility and acceptability. Participants in the intervention group will track their daily dietary intake for the duration of the intervention using paper and/or RedCap surveys. These surveys will be reviewed weekly by the health coach for completeness before being analyzed with NDSR (NDSR, Nutrition Coordinating Center, University of Minnesota, MN). To account for deviations from the meal plan, overall dietary compliance will be evaluated by comparing participant’s Healthy Eating Index (HEI) score to that of the standard meal plan. Participants will track their adherence to the exercise intervention (150 min/wk. exercise) using personal training software (FitSW, FitSW Inc., Colorado Springs, CO) and their steps will be continuously monitored by a pedometer (Fitbit, Garmin, Apple Watch, etc.) provided by the research team. Compliance with the exercise prescription (150 min/week) and walking goal (500 extra steps/week) will be assessed weekly by the health coach. Coaches will document the average number of weekly steps and total exercise minutes.

#### Data management

All investigators and research team members will complete and maintain appropriate CITI training. All data will be entered into the ACNC clinical relational database and/or RedCap. The database will be housed on a shared drive that is backed up nightly off-site Monday through Friday. Access to the server is password protected, as is access to the study database. Data and study samples will be labeled with a unique identifier (e.g., MB-101). This identifier will be in no way associated with the participant’s personal information, such as name or date of birth. The key to the coded information, all identifiers, and biological specimens will be destroyed 7 years after the study close date. Data and samples will not be used for future research, either with or without identifiers. Participant names, contact information, and address will be shared with the meal preparation and delivery company. Data and samples will only be accessible by investigators, research assistants, and institutional oversight offices (e.g., IRB).

#### Statistical analyses

Prior to inferential analyses, exploratory data methods will be used to check for potential outliers and aberrant observations and measurements. The following will be tested between the PCOS and no PCOS groups to assess potential differences: fertility diagnosis (male factor, ovulatory disorder, tubal factor, endometriosis or unexplained), pregnancy, live birth, age and race using Mann-Whitney U nonparametric tests for each strata. Follicular fluid and serum metabolites will be analyzed using a one factor Analysis of Covariance (ANCOVA) at four levels because of the potential unbalanced data structure. Pair-wise comparisons using Tukey-Kramer post-hoc tests will be used to identify groups whose means differ significantly while retaining the family-wise error rate at 5%. If the distributional assumptions for ANOVA are not met, and if a suitable data transformation is not found, a Kruskal-Wallis equality-of-populations rank test will be used, followed by Dunn’s test of multiple comparisons. When the design is balanced, two-way ANOVA or non-parametric Friedman test will be used in data analysis. As alternatives, generalized linear models may be also used to test the effects of treatment and presence of PCOS and ANCOVA may also be used to control for additional confounding factors Correlations will be determined using the Pearson Product Moment or the Spearman Rank Order for non-parametric tests. Significance will be set at *p* < 0.05. RNA-seq data will be analyzed using SeqMonk and R software. Gene expression levels will be expressed as raw read counts for differential expression analysis and as log-transformed normalized reads per kilobase per million mapped reads for visualization. Differentially expressed gene expression will be identified using the DESeq2 package and filtered at ± two-fold change and statistical significance with a *p* value ≤0.05. Gene Ontology (GO), transcription factor (TF) target analysis, and pathway analyses will be conducted with DAVID bioinformatics and/or WebGestalt, which include multiple testing corrections. For participants assigned to the standard of care whose fertility treatments were unsuccessful, they will be offered to re-enroll and be directly assigned to the intervention group. The data from these participants will be analyzed separately, using paired t-tests or non-parametric equivalent to evaluate the effect of the intervention (pre and post).

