**Methods:**

This single blinded randomized control trial will include 120 women with a BMI of 25–45 kg/m^2^, ≥21 years of age, and undergoing in vitro fertilization (IVF) treatments. Participants will be randomized to standard of care (*N* = 60) or an intervention group (*N* = 60) in a block design by polycystic ovary syndrome status. The intervention will combine a dietary component (Mediterranean meal plan) with exercise prescription following the Physical Activity Guidelines for Americans. Participants will be assessed pre- and post-intervention. The standard of care group will be offered to join the intervention group if the IVF treatments are unsuccessful as a cross over design. Recruitment is anticipated to start in July of 2021. Primary outcomes will include single oocyte gene expression profiles and follicular fluid metabolites. Mann-Whitney U nonparametric tests will be used to assess potential differences for each stratum. Follicular fluid and serum metabolites will be analyzed using a one-factor Analysis of Covariance (ANCOVA) at four levels, pair-wise comparisons using Tukey-Kramer post-hoc tests will be used to identify groups whose means differ significantly while retaining the family-wise error rate at 5%. When the design is balanced, two-way Analysis of Variance (ANOVA), or non-parametric Friedman test will be used in data analysis. Additionally, general linear models and ANCOVA may be used to control for covariates. Significance will be set at *p* < 0.05. Findings will be disseminated via peer-reviewed manuscripts and presentations at scientific conferences.

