### Consent and randomization

The informed consent process will educate potential participants about the research study through IRB-approved methods. Eligible participants will be contacted, and a copy of the informed consent will be provided to the participant prior to signing consent documents. A research team member will reach out to potential participants 2 days prior to the scheduled visit to perform a COVID-19 screening and answer questions on the intervention components of the study. At the first visit, the research team will review all study procedures and the informed consent documents with the potential participant. Participants will be given sufficient time to review the consent form, ask questions, and receive clarification prior to signing any documents. If eligible and interested in enrollment, informed consent will be obtained from the participants and documented.

Women will be randomized, with computer generated randomization, to a standard of care group (*N* = 60) and an intervention group (*N* = 60). Due to the high incidence of obese women with Polycystic Ovarian Syndrome (15–30%) [26], compared with other infertility diagnoses, women will first be classified into one of two strata based on the presence or absence of PCOS. Within each stratum, the proposed study will randomize the enrolled participants into either the intervention group (*N* = 30) or the standard of care group (*N* = 30). Thus, the potential for confounders of infertility, besides PCOS, should be equally distributed between the groups and not affecting the main outcome of interests. The study will have four experimental arms: PCOS-standard of care, PCOS-intervention, no PCOS-standard of care, no PCOS-intervention. Allocation will happen at the second visit (after consent and the collection of baseline measures) by providing the participant with an opaque, sealed envelope containing their allocation.

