#### Sample size

Based upon existing data in the literature, a power of 0.8, and a *p*-value set at 0.05, with 20 women per group, we will be able to detect a mean difference of at least 0.37 standard deviation units in follicular levels of C-reactive protein and of insulin. In our previous study, we found follicular fluid CRP differences of 3.2 μg/ml (2.7 vs. 5.9 μg/ml, respectively) between normal weight and obese women [12]. Thus, we are confident that this sample size will be sufficient to detect clinically meaningful differences. Based on our experience, we expect that we will be unsuccessful in obtaining a good quality oocyte from approximately 33% of women enrolled. Therefore, we will enroll 30 women in each of the 4 groups (PCOS- standard of care, PCOS-intervention, no PCOS- standard of care, no PCOS-intervention) to assure that we will have at least 20 oocytes per group.

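### Mann-Whitney U is assigned to unordered fertility diagnosis and race, and the same sentence leaves unclear whether PCOS strata or randomised arms are compared

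*Protocol article*

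**What the plan says.** In the Statistical analyses section, the sentence on preliminary comparisons opens with "The following will be tested between the PCOS and no PCOS groups to assess potential differences". It then names "fertility diagnosis (male factor, ovulatory disorder, tubal factor, endometriosis or unexplained" as the first variable and ends with "pregnancy, live birth, age and race using Mann-Whitney U nonparametric tests for each strata". The threshold is given in the same section: "Significance will be set at *p* < 0.05".

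The Methods paragraph of the abstract carries a shorter form, with neither the variables nor the PCOS contrast: "Mann-Whitney U nonparametric tests will be used to assess potential differences for each stratum".

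Consent and randomization defines the stratum: "women will first be classified into one of two strata based on the presence or absence of PCOS". Allocation then takes place inside it: "Within each stratum, the proposed study will randomize the enrolled participants into either the intervention group" or standard of care. Sample size gives the numbers: "we will enroll 30 women in each of the 4 groups". That makes 60 women with PCOS and 60 without.

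The primary outcomes are oocyte gene expression and follicular fluid metabolites. The secondary objectives are cumulus cell expression, feasibility and acceptability. Pregnancy and live birth appear in neither list. They are nevertheless collected: Table 1 has birth outcomes at retrieval, and the medical release covers pregnancy and delivery outcomes.

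**The concern.** Three things in one sentence need attention.

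- **Test.** Mann-Whitney ranks the observations. Male factor, ovulatory disorder, tubal factor, endometriosis and unexplained infertility cannot be ranked, and neither can race. The software will rank whatever integer codes the database uses, so the p value reflects the code list. A real imbalance can be missed.
- **Contrast.** Inside a PCOS stratum every woman has the same PCOS status, so a PCOS comparison cannot be made separately in each stratum. Two statisticians could run different analyses from this sentence.
- **Post-randomisation outcomes.** On the literal contrast, pregnancy and live birth are compared by a pre-existing characteristic. Such a comparison carries no information about the intervention, yet these are the clinical results that readers of a trial in women undergoing IVF will look for.

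**Working it through.** The plan gives no figure for this point, so there is none to reproduce. The group sizes (60 versus 60) follow from the plan: 2 × 30 = 60 per PCOS stratum. All category counts and event counts below are assumptions. Sidedness is not stated; two-sided tests are used. Mann-Whitney is the tie-corrected normal approximation without continuity correction.

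**1. Dependence on coding, five-category diagnosis.**

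Assumed counts, in the order in which the protocol lists the diagnoses: 18, 6, 12, 12, 12 in one stratum and 6, 30, 9, 9, 6 in the other.

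With equal group sizes, Pearson chi-square = Σ (a − b)² / (a + b):

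12²/24 + 24²/36 + 3²/21 + 3²/21 + 6²/18 = 6 + 16 + 0.429 + 0.429 + 2 = 24.86 on 4 degrees of freedom, p = 0.00005.

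This value does not change when the categories are relabelled. Mann-Whitney does change. There are 5! = 120 ways to assign the codes, and all were run on the same table. A second assumed table (12, 24, 6, 6, 12 versus 21, 6, 9, 9, 15) was run as a check. Its chi-square is 9²/33 + 18²/30 + 3²/15 + 3²/15 + 3²/27 = 2.455 + 10.8 + 0.6 + 0.6 + 0.333 = 14.79.

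| Assumed table | Chi-square p | Mann-Whitney p, smallest | Mann-Whitney p, largest | Mann-Whitney p, order as listed |
|---|---|---|---|---|
| First | 0.00005 | 0.000003 | 0.70 | 0.44 |
| Second | 0.005 | 0.001 | 0.85 | 0.85 |

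In the second table, half of the 120 codings fall below 0.05. In 2,000 simulated trials with the category shares of that table, Mann-Whitney rejected in 5.8% with the listed order and in 93% with the most favourable order; chi-square rejected in 91%.

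**2. Binary outcomes.**

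For a yes/no variable the tie-corrected statistic satisfies z² = (N − 1)/N × Pearson chi-square. With N = 120 the factor is 119/120 = 0.9917. For 15/60 versus 26/60, chi-square = 4.483 and z² = 4.483 × 0.9917 = 4.446.

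| Events (of 60 vs 60) | Mann-Whitney p | Chi-square p |
|---|---|---|
| 15 vs 26 | 0.0350 | 0.0342 |
| 18 vs 27 | 0.0910 | 0.0897 |
| 20 vs 30 | 0.0652 | 0.0641 |

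The choice of test is therefore immaterial for pregnancy and live birth.

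**3. The contrast, place by place.**

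| Place | What is compared |
|---|---|
| Consent and randomization | Stratum = PCOS yes/no; randomised arms lie within the stratum |
| Statistical analyses, opening of the sentence | PCOS versus no PCOS |
| Statistical analyses, end of the sentence | Something within each stratum, so it cannot be PCOS status |
| Abstract, Methods | Something within each stratum, unnamed |

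The opening of the sentence rules out an analysis within strata, and its end rules out the PCOS contrast. The plan does not say which prevails.

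**The case against.** The strongest reply is that little hangs on this sentence. None of the five variables is a listed primary or secondary outcome. Treatment comparisons for the main outcomes are provided elsewhere in the section: a four-level ANCOVA whose Tukey-Kramer pairs include intervention versus standard of care within each stratum, and DESeq2 for expression. Generalized linear models with treatment and PCOS effects are allowed as an option, and that permission is not expressly confined to metabolites. Describing how the strata differ in age, race and diagnosis is a legitimate aim. The counts used above are invented. All of this stands, and it lowers the rank of the point. It does not rescue a rank test on unordered categories, because dependence on coding is a property of the test and not of the counts.

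A reader might infer two stronger claims, and the document supports neither.

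- *That Mann-Whitney is also the wrong test for pregnancy and live birth.* It is unusual for binary data, but it is practically the chi-square test.
- *That the trial has settled on no randomised comparison of pregnancy and live birth.* The abstract's wording leaves open a comparison of arms within each stratum, and a condensed article may leave the analysis of unlisted outcomes to the full protocol or analysis plan. What is established is that the only contrast spelled out for these outcomes is PCOS status, in a sentence that conflicts with itself.

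**Conclusion.** The point holds in this form, as something that should be fixed.

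- For diagnosis, and for race if it is recorded in more than two categories, the named test gives an arbitrary p value. In the first assumed table it ranged from 0.000003 to 0.70 on identical data. The width of that range depends on the assumed counts; the arbitrariness does not.
- The contrast is undetermined, because the sentence names PCOS status and also calls for analysis within PCOS strata, and the abstract keeps only the second half.
- Taken literally, pregnancy and live birth are contrasted by stratum and not by arm, which does not inform on the intervention.

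The primary comparisons are not affected, so a higher rank is not justified.

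**What to change.** Rewrite the sentence and the matching line of the abstract so that both state one contrast:

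- **Diagnosis and race:** tabulate them; if a test is wanted, use chi-square or a Fisher-type exact test. A descriptive comparison of age, race and diagnosis between women with and without PCOS may remain, labelled as such.
- **Age:** keep Mann-Whitney.
- **Pregnancy and live birth:** compare intervention with standard of care, stratified by or adjusted for PCOS, for example by Cochran-Mantel-Haenszel or a logistic model with treatment and PCOS. Standard-of-care women who re-enrol into the intervention stay out of this comparison, as the section already provides by analysing them separately.

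The cost is wording only: no change to the sample size, the visits or the data collected.

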### Eligibility and recruitment

Criteria for study inclusion are women with a BMI between 25 and 45 kg/m^2^, age of 21 years or over, and planning to undergo in vitro fertility treatment. Participants reporting the following will be excluded from the study: pre-existing conditions (e.g. sexual transmitted diseases) that will affect the outcomes of the study as determined by the principal investigator; current use of recreational drugs, tobacco, nicotine, or alcohol; food allergies, food intolerances, or food preferences which would interfere with compliance to the meal plan; and contraindications to exercise or already meeting the Physical Activity Guidelines for Americans [8] (150 min moderate activity/week or 75 min of vigorous activity/week with resistance exercise on 2 or more days/week.

Recruitment of participants will be conducted by the AF&GA team using IRB-approved tools. Advertisements and information sheets will be distributed to eligible participants electing to undergo fertility treatments. Women who are interested in participating in the study can inform the AF&GA team, call the ACNC recruitment line, send an e-mail expressing their interest, or express their interest through the ACNC website. To establish eligibility for participation in the study, a standardized questionnaire will be administered by phone.

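### The models fixed for serum and follicular fluid metabolites name no baseline covariate and leave adjustment optional, although Visit 1 BMI and serum analytes are collected before allocation

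*Protocol article*

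**What the plan says.** The Statistical analyses section of the protocol article sets out the metabolite analysis: "Follicular fluid and serum metabolites will be analyzed using a one factor Analysis of Covariance (ANCOVA) at four levels" (the sentence goes on to give a possibly unbalanced data structure as the reason). The four levels are the treatment-by-PCOS cells defined under Consent and randomization. Tukey-Kramer comparisons follow. If assumptions fail and no transformation helps, Kruskal-Wallis with Dunn's test is used. If the design is balanced, two-way ANOVA or Friedman is used.

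Adjustment enters only among the alternatives: "ANCOVA may also be used to control for additional confounding factors". The abstract is equally open: "general linear models and ANCOVA may be used to control for covariates". Neither place names a covariate.

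On the data available:
- Eligibility admits "women with a BMI between 25 and 45 kg/m^2".
- Table 1 marks anthropometrics at Visits 1 and 3.
- The Biological samples section says that fasting blood "will be collected from the participants at visits 1 and 3 by a trained phlebotomist".
- Allocation takes place at Visit 2, after baseline measures.
- Glucose, total cholesterol, triglycerides, insulin, leptin, TNF-α, CRP and IL-6 are assayed in both serum and follicular fluid.
- Follicular fluid is collected only at oocyte retrieval.

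**The concern.** An analysis of covariance needs a covariate, and unbalanced cell sizes are not a reason to use one. Taken literally, the stated model is a one-way ANOVA on four cells; the fallback sentence itself speaks of ANOVA assumptions. None of the branches the article commits to carries a baseline value. The only pre/post analysis described is the paired test for standard-of-care women who re-enrol into the intervention.

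Two things are at stake. First, differences between women that are known before randomisation stay in the error term, in a trial with 20 to 30 women per cell. Second, because adjustment is optional and the covariates are unnamed, the choice between an adjusted and an unadjusted result can be made after the data are seen.

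The article gives some reason to expect BMI to be prognostic. Its Sample size section reports follicular CRP of 2.7 against 5.9 μg/ml "between normal weight and obese women". BMI may span 20 units in this trial and is not a stratification factor.

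**Working it through.** **Inputs from the article.** Power 0.8, p-value 0.05 (taken as two-sided), 20 women per group after an expected 33% loss for oocyte quality, and 30 enrolled per group in four groups. **Assumed:** rho, the correlation of the outcome with the baseline covariates, at 0.1, 0.3, 0.5 and 0.7. The article gives no value.

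**Step 1: the plan's own figure.** The Sample size section says that 20 per group detects 0.37 SD. For two groups the normal approximation gives

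d = (1.960 + 0.842) × √(2/20) = 0.886 SD,

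and the t-test gives 0.909 SD. The stated 0.37 SD is not reproduced as a mean difference, so 0.909 is used as the unadjusted baseline below. The enrolment step does reproduce: 20 / (1 − 0.33) = 29.9, rounded up to 30.

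**Step 2: effect of adjustment.** Residual variance is multiplied by (1 − rho²). The detectable difference is therefore multiplied by √(1 − rho²), and the equivalent sample size by 1/(1 − rho²). The loss of about 2 degrees of freedom is ignored here.

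| rho | Variance reduction | Equivalent sample size | 20 per group: detectable SD | 30 per group: detectable SD |
|---|---|---|---|---|
| 0 | 0% | 1.00 | 0.91 | 0.74 |
| 0.1 | 1% | 1.01 | 0.90 | 0.73 |
| 0.3 | 9% | 1.10 | 0.87 | 0.70 |
| 0.5 | 25% | 1.33 | 0.79 | 0.64 |
| 0.7 | 49% | 1.96 | 0.65 | 0.53 |

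Example: 0.909 × √(1 − 0.25) = 0.787.

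**Step 3: which group size applies.** The figure of 20 allows for women without a good-quality oocyte. The section on oocyte, cumulus cell and follicular fluid collection says that follicular fluid is still obtained when no spare oocyte is available. The number for metabolites may therefore lie nearer 30 per cell, less drop-outs and blood-contaminated samples, and the 30-per-group column is shown for that reason.

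**Step 4: what adjustment cannot do.** To bring 0.909 SD down to 0.37 SD would need rho² = 1 − (0.37/0.909)² = 0.83, that is rho of about 0.91. Adjustment does not rescue the sample-size statement.

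All detectable differences here are for a single two-group comparison. With Tukey-Kramer control over four groups of 20, the unadjusted pairwise figure is about 1.10 SD. It shrinks by the same factor √(1 − rho²).

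**The case against.** A fair defence has four parts.

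- **Silence is not exclusion.** The article names an ANCOVA without listing covariates, and its reference to additional confounders could imply that some are already in the model. A fuller protocol or a SAP may list them. This stands against the stronger inference that baseline values will not be used: the article does not say so. It does not remove the point, because the article commits to a sequence of models and makes adjustment discretionary. That is more than leaving out a list.
- **Follicular fluid has no baseline.** This stands. Only serum can be adjusted for its own earlier value. For follicular fluid, the primary fluid, BMI and Visit 1 serum are proxies, the latter from a different fluid and usually 8 to 12 weeks earlier.
- **The size is unknown.** This also stands. The CRP contrast suggests that weight matters, but it includes normal-weight women, whom this trial excludes, and it gives no correlation within BMI 25 to 45. A reader might infer from the top of the range that the trial forgoes the equivalent of nearly twice as many women. Nothing in the document supports a rho of 0.7, and at 0.1 the gain is 1%.
- **Validity is intact.** This stands. Randomisation makes the unadjusted comparison unbiased, and the text permits adjustment, so it would be wrong to say that chance BMI imbalance must go uncorrected.

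**Conclusion.** The point holds in this form: the committed models name no baseline covariate, the label ANCOVA rests on a reason that does not justify it, and adjustment is optional although suitable pre-allocation data are collected. It is a matter of efficiency and pre-specification, not of bias.

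The gain is conditional on rho, for which the document gives no figure. At low rho it is negligible; at moderate rho it is useful. It is likely to be larger for serum, where the covariate is the same analyte in the same fluid, than for follicular fluid. The step from 20 to 30 per cell moves the unadjusted detectable difference by 0.17 SD (0.91 to 0.74), more than adjustment at rho 0.5 does with 20 per group (0.12 SD). The absolute figures should therefore be read with the achieved sample size in mind. The change is still worth making because it costs almost nothing.

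**What to change.** State one primary model for each fluid and replace the optional wording with it:

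- **Serum:** Visit 3 value as outcome; treatment, PCOS stratum, Visit 1 value of the same analyte and Visit 1 BMI as terms.
- **Follicular fluid:** value at retrieval as outcome; treatment, PCOS stratum, Visit 1 BMI and the matching Visit 1 serum analyte as proxy covariates.
- Use the log scale for skewed analytes.

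Writing treatment and PCOS stratum as separate terms replaces the four-level factor and is a change in its own right. If the four-cell comparison is to be kept, the same two covariates can be added to it. If no covariate is wanted, call the model ANOVA and drop the imbalance rationale.

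The cost is a change of analysis wording and about 2 degrees of freedom, with no new data collection.
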